## Abstract

**Background:**

The combination of nivolumab, a programmed death-1 (PD-1) targeted monoclonal antibody, with the cytotoxic T-lymphocyte antigen-4 (CTLA-4) targeted antibody, ipilimumab, represents a new standard of care in the first-line setting for patients with intermediate- and poor-risk metastatic renal cell carcinoma (mRCC) based on recent phase III data. Combining ipilimumab with nivolumab increases rates of grade 3 and 4 toxicity compared with nivolumab alone, and the optimal scheduling of these agents when used together remains unknown. The aim of the PRISM study is to assess whether less frequent dosing of ipilimumab (12-weekly versus 3-weekly), in combination with nivolumab, is associated with a favourable toxicity profile without adversely impacting efficacy.

**Methods:**

The PRISM trial is a UK-based, open label, multi-centre, phase II, randomised controlled trial. The trial population consists of patients with untreated locally advanced or metastatic clear cell RCC, and aims to recruit 189 participants. Participants will be randomised on a 2:1 basis in favour of a modified schedule of 4 doses of 12-weekly ipilimumab versus a standard schedule of 4 doses of 3-weekly ipilimumab, both in combination with standard nivolumab. The proportion of participants experiencing a grade 3 or 4 adverse reaction within 12 months forms the primary endpoint of the study, but with 12-month progression free survival a key secondary endpoint. The incidence of all adverse events, discontinuation rates, overall response rate, duration of response, overall survival rates and health related quality of life will also be analysed as secondary endpoints. In addition, the potential of circulating and tissue-based biomarkers as predictors of therapy response will be explored.

**Discussion:**

The combination of nivolumab with ipilimumab is active in patients with mRCC. Modifying the frequency of ipilimumab dosing may mitigate toxicity rates and positively impact quality of life without compromising efficacy, a hypothesis being explored in other tumour types such as non-small cell lung cancer. The best way to give this combination to patients with mRCC must be similarly established.

**Trial registration:**

PRISM is registered with ISRCTN (reference ISRCTN95351638, 19/12/2017).

**Trial status:**

At the time of submission, PRISM is open to recruitment and data collection is ongoing.

## Background

Kidney cancer is the 14th most common cancer worldwide with an estimated 400,000 new cases, and 175,000 attributable deaths, in 2018 [1]. The majority of kidney cancers (90%) are renal cell carcinomas (RCC), most of which (75%) are of the clear cell subtype [2].

For the past decade, the mainstay of treatment for patients with metastatic RCC (mRCC), has been in the form of small molecule, vascular endothelial growth factor receptor-targeted, tyrosine kinase inhibitors (VEGFR TKIs), such as sunitinib and pazopanib. Whilst most patients initially get a clinical benefit from VEGFR TKIs, acquired resistance is typically observed within months after starting therapy, with median overall survival (OS) in the region of 2 years [3, 4]. The introduction of checkpoint inhibitors, targeting the cytotoxic T-lymphocyte antigen 4 (CTLA-4) and programmed death-1 (PD-1) T-cell receptors, has transformed the treatment landscape for patients with mRCC. The anti-PD1 antibody nivolumab, for example, is a standard treatment option following failure of VEGFR TKI [5].

Recently (during the set-up of PRISM), initial results from the landmark phase III trial, CheckMate 214 (CM214) comparing nivolumab plus the anti-CTLA-4 antibody ipilimumab against standard of care sunitinib, have been reported. In total, 1096 participants with untreated metastatic clear cell RCC were randomised 1:1 to receive either sunitinib (50 mg 4 weeks on; 2 weeks off) or combination immunotherapy using a schedule of nivolumab 3 mg/kg (N3) plus ipilimumab 1 mg/kg (I1) every 3 weeks for 4 doses, followed by nivolumab 3 mg/kg every 2 weeks until disease progression or toxicity warranting treatment discontinuation [6]. Amongst the 77% of participants with intermediate- or poor-risk disease, as per International Metastatic Renal Cell Carcinoma Database Consortium (IMDC) criteria [7], median OS was not reached in the N3 + I1 arm and was 26.0 months in the sunitinib arm (HR 0.63, *p* < 0.001), establishing the combination as a new standard of care for the first-line treatment of patients with intermediate- and poor-risk mRCC [8]. Efficacy amongst favourable-risk participants formed an exploratory endpoint of the study and suggests improved response rates and PFS amongst sunitinib-treated patients, although these results should be interpreted with caution given the immature nature of the survival data and small sample size (*n* = 249). The reported toxicity associated with N3 + I1 was, however, significant. The rate of grade 3 or 4 treatment-related adverse events (AE) was 46% and led to treatment discontinuation in 22% of participants receiving the combination. In addition, high dose glucocorticoids (≥ 40 mg prednisone per day) were required in 35% of participants in order to manage immune-related AEs [6]. Until recently this combination treatment was not available in the UK, however it has gained approval for use in England through the national Cancer Drugs Fund in early April 2019 [9].

### Study rationale

Whilst CM214 has established the superior efficacy of combination nivolumab with ipilimumab over sunitinib in patients with intermediate- and poor-risk mRCC, optimal scheduling of these drugs has not been explored in this disease area. Additionally, improving our current understanding of why some patients respond to immunotherapy whilst many others derive no benefit is recognised as a research priority and translational studies focusing on predictive biomarkers forms a further important exploratory objective of the trial.

PRISM is a Phase II, open label, multi-centre, parallel group, randomised controlled trial. Our trial was designed before CM214 results were available and seeks to establish whether less frequent scheduling of ipilimumab is associated with improved tolerability in patients with mRCC in comparison to the schedule used in CM214, without adversely impacting activity (in comparison with historic control data).

Studies in other cancer types demonstrate ipilimumab dose and / or frequency can affect the toxicity and efficacy of treatment. In advanced melanoma, for example, 10 mg/kg ipilimumab every 3 weeks for 4 doses was associated with longer median OS but higher rates of grade 3 or 4 toxicity, in comparison to 3 mg/kg dosing [10]. A recently reported melanoma trial comparing I3 + N1 versus I1 + N3 again showed a favourable toxicity profile associated with a lower dose of ipilimumab, with no apparent difference in efficacy at a minimum follow-up of 12 months [11]. Varying doses and schedules of ipilimumab plus nivolumab have also been examined amongst 8 cohorts within the phase Ib CM012 study in patients with non-small cell lung cancer, including nivolumab 3 mg/kg q2W plus ipilimumab 1 mg/kg given either 6- (*n* = 39) or 12- (*n* = 38) weekly [12]. The schedule N3 (2-weekly) + I1 (6-weekly) was selected for phase III evaluation based on its safety and efficacy profile [13]. Thus, formal investigation of the scheduling of ipilimumab when given in combination with nivolumab in patients with mRCC is warranted.

It was not feasible to design the study for an internal comparison of efficacy given the phase II nature of the trial and the required sample size for such a comparison. As the trial was designed prior to CM214 results being available, PRISM is powered to compare activity of the modified schedule with historic sunitinib control data, however ancillary analyses will explore results in relation to CM214.

## Methods

### Trial objectives

#### Primary objective

The primary aim of the PRISM trial is to assess whether the proposed alternative scheduling of ipilimumab (12-weekly), when given in combination with nivolumab, warrants further consideration based on safety and efficacy, as defined by the proportion of participants experiencing a grade 3 or 4 adverse reaction (AR) within 12 months and 12-month progression-free survival (PFS).

#### Secondary objectives

Secondary objectives include assessment in each treatment arm of: incidence of adverse reactions; treatment discontinuation rates; overall response rate; duration of response; response rate post-progression (for those receiving treatment beyond progression); overall survival rates; and health-related quality of life (HR-QoL).

#### Exploratory objectives

To explore circulating and tissue-based predictive biomarkers of response to immunotherapy.

### Trial design

The study protocol and this manuscript have been written in accordance with standard protocol items: recommendations for interventional trials (SPIRIT) guidelines [14]. We have included a SPIRIT checklist as supplementary material (Additional file 1: Table S1).

The PRISM trial is an open label, multi-centre, phase II, randomised controlled trial to explore the efficacy and safety of alternative reduced intensity scheduling of ipilimumab, when given in combination with nivolumab as first-line therapy, in patients with locally advanced or metastatic RCC. The trial will recruit 189 participants with individual randomisation on a 2:1 basis in favour of the modified schedule (see Fig. 1). The two arms of the trial are as follows (see Fig. 2):
Arm A (modified schedule): 3 mg/kg nivolumab plus 1 mg/kg of ipilimumab every 12 weeks for 4 doses with:
2-weekly 240 mg flat dose single agent nivolumab between the first and second combined doses, and4-weekly single agent nivolumab between the second and third, and third and fourth combined dosesFollowed by 4-weekly 480 mg flat dose single agent nivolumab following the fourth combination dose, until disease progression/unacceptable toxicity/participant choice.Arm B (standard schedule): 3 mg/kg nivolumab intravenously plus 1 mg/kg of ipilimumab every 3 weeks for 4 doses. Followed by 4-weekly 480 mg flat dose single agent nivolumab following the fourth combination dose, until disease progression/unacceptable toxicity/participant choice.

**Fig. 1 Fig1:**
[figure not shown]
PRISM trial schema

**Fig. 2 Fig2:**
[figure not shown]
Treatment schedule. Frequency and dosing of nivolumab and ipilimumab for both arms of the study are shown

Participants may receive treatment beyond first Response Evaluation Criteria In Solid Tumors (RECIST) v1.1 [15] defined progression based on investigator-assessed clinical benefit, tolerance of study drugs and stable performance status, as a minority of patients treated with immunotherapy may derive clinical benefit despite initial evidence of progressive disease. Trial treatment will be discontinued permanently upon documentation of further progression defined as the presence of any new lesion or an additional 10% increase in existing tumour burden from time of initial progression. Treatment will also be discontinued if treatment is delayed or interrupted for more than 6 weeks.

#### Quality of life evaluation

It is thought that nivolumab plus 12-weekly ipilimumab could be associated with favourable HR-QoL in comparison to standard 3-weekly dosing of ipilimumab. In order to evaluate treatment tolerability and its impact from a patient perspective, Patient-Reported Outcome Measures (PROM) to evaluate both overall HR-QoL and patient-reported AEs (physical symptoms of RCC and side effects of the treatments) will be collected. The severity and trajectory of AEs (symptoms or side-effects) of both treatment schedules will be reported, allowing comparison between clinician reported AEs (CTCAE V5.0) and patient-reported AEs using PROMs [16]. The primary outcome measure will be the summary score for HR-QoL of European Organisation for Research and Treatment of Cancer (EORTC) QLQ-C30. Secondary descriptive outcomes will include EQ-5D-5L™, physical symptoms of RCC (measured by Functional Assessment of Cancer Therapy Kidney Symptom Index (FKSI-19)) and known side-effects of ipilimumab and nivolumab measured by selected items from EORTC Quality of Life Group item bank [17]. We propose to use the item bank approach to cover expected toxicity of the investigational treatments, as due to the rapid introduction of new targeted cancer treatments there are no existing validated instruments that will cover the full range of AEs and using well developed and validated items from the item bank is a viable rapid alternative. PRO measures will be collected at baseline, weeks 7 and 13, then 12-weekly. The data collection will stop at disease progression or 61 weeks, whichever is earlier.

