#### During treatment

Due to the difference in treatment schedules, participants in Arm A (modified schedule) will be assessed every 2 weeks for the first 12 weeks while those in Arm B (standard schedules) will be assessed every 3 weeks until week 16. Thereafter, all participants will be assessed 4-weekly. Each assessment will include: clinical assessment; adverse event reporting; LFTs; FBC; U&Es; thyroid function test (TFT); glucose; calcium; amylase; and cortisol. PROMs will be completed at baseline and weeks 7, 13, and then 12-weekly until 61 weeks or until disease progression, whichever is earlier. Assenting participants will give samples of serum and plasma (and at selected sites only, PMBCs) at baseline, weeks 7, 13 and at disease progression.

The differential reporting between trial arms is not felt to be a large concern due to: i) the short time lapse between assessments; ii) there being only 1 week’s difference in the reporting period between trial arms; iii) follow-up being 4-weekly for both trial arms for the majority of the trial; and iv) the primary and key secondary endpoints being over 12 months. In addition, this differential follow-up is in favour of the standard schedule (Arm B) due to more frequent reporting in Arm A (modified schedule), and is therefore conservative.

All participants will receive radiological assessment according to RECIST criteria using contrast enhanced CT of the chest, abdomen and pelvis every 12 weeks until disease progression or treatment discontinuation (whichever occurs later).

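### From week 13 the 12-weekly questionnaires run in phase with Arm A's ipilimumab doses, so short-lived patient-reported effects of its doses 2 to 4 go unobserved

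*Protocol article*

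**What the plan says.** Trial design sets the ipilimumab schedules. Arm A receives "3 mg/kg nivolumab plus 1 mg/kg of ipilimumab every 12 weeks for 4 doses"; Arm B receives "1 mg/kg of ipilimumab every 3 weeks for 4 doses" alongside nivolumab.

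Quality of life evaluation gives a single questionnaire calendar for both arms: "PRO measures will be collected at baseline, weeks 7 and 13, then 12-weekly". It adds that "The data collection will stop at disease progression or 61 weeks, whichever is earlier". The During treatment section repeats this: "PROMs will be completed at baseline and weeks 7, 13, and then 12-weekly until 61 weeks or until disease progression, whichever is earlier".

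The purpose is comparative and has an expected direction: "It is thought that nivolumab plus 12-weekly ipilimumab could be associated with favourable HR-QoL in comparison to standard 3-weekly dosing of ipilimumab". The same section undertakes to report how severe side effects are and how they evolve under both schedules, and to compare patients' reports with clinicians' CTCAE grading.

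The During treatment section discusses unequal assessment between arms and calls it conservative. That argument concerns how often participants attend clinic. It does not consider when questionnaires fall in relation to dosing.

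**The concern.** The questionnaire interval from week 13 equals Arm A's ipilimumab interval, and the two start together. Each Arm A questionnaire from week 13 to week 37 is therefore due in the week of the next ipilimumab dose, and nothing is asked in between. Arm B's four doses are compressed into the first ten weeks, where questionnaires at weeks 7 and 13 fall close behind them.

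Two things are at stake. First, the course of side effects after three of Arm A's four ipilimumab doses cannot be described from readings taken only at the end of each interval. Clinicians assess 4-weekly over the same period, so agreement between patients and clinicians may differ by arm purely because of the calendar. Second, if ipilimumab symptoms come early and fade, they are captured in Arm B and largely missed in Arm A, which is the direction the trial expects. No later analysis can recover data that were not collected.

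**Working it through.** **Inputs.** Dosing comes from Trial design, questionnaire weeks from Quality of life evaluation and During treatment, and visit patterns from During treatment.

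**Questionnaire calendar.** Weeks 7 and 13, then 13 + 12k for k = 1 to 4, gives 7, 13, 25, 37, 49 and 61. The last value reproduces the stated 61 weeks.

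**Week numbering.** The article does not say whether the first dose is week 0 or week 1. Arm A "will be assessed every 2 weeks for the first 12 weeks" and Arm B "will be assessed every 3 weeks until week 16". With the first dose in week 1, visits are at weeks 1, 3, 5, 7, 9, 11, 13 (Arm A) and 1, 4, 7, 10, 13, 16 (Arm B). Weeks 7 and 13 are then visits in both arms, as the Translational study section says of the blood samples due in those weeks, and week 16 is an Arm B visit. With the first dose in week 0, visits fall at weeks 0, 2, ..., 12 and 0, 3, ..., 15, and none of this holds. Week 1 is the reading that fits.

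**Dose weeks.** Arm A: 1 + 12k = 1, 13, 25, 37. Arm B: 1 + 3k = 1, 4, 7, 10 (k = 0 to 3).

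**Weeks from each dose to the next later questionnaire.**

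| Dose | Arm A | Arm B |
|---|---|---|
| 1 | 7 − 1 = 6 | 7 − 1 = 6 |
| 2 | 25 − 13 = 12 | 7 − 4 = 3 |
| 3 | 37 − 25 = 12 | 13 − 7 = 6 |
| 4 | 49 − 37 = 12 | 13 − 10 = 3 |

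**Weeks since the last earlier ipilimumab dose, at each questionnaire** (a dose due in the same week is not counted).

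| Week | 7 | 13 | 25 | 37 | 49 | 61 |
|---|---|---|---|---|---|---|
| Arm A | 6 | 12 | 12 | 12 | 12 | 24 |
| Arm B | 3 | 3 | 15 | 27 | 39 | 51 |

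**Direction, by illustration.** The article gives no symptom time course, so the following are assumptions. Each dose adds one unit of burden over a fixed window, identical in both arms. True total burden is 4 × duration in each arm. The questionnaire estimate is the trapezoidal area over weeks 1 to 61, with baseline set to 0 at week 1.

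- *Starts at dosing, lasts 5 weeks (true total 20).* Arm A reads 0 throughout, area 0. Arm B reads 1 at weeks 7 and 13: 3 + 6 + 6 = 15. This favours Arm A.
- *Starts at dosing, lasts 8 weeks (true total 32).* Arm A reads 1 at week 7 only: 3 + 3 = 6. Arm B reads 2 at weeks 7 and 13: 6 + 12 + 12 = 30. This favours Arm A.
- *Starts at dosing, lasts 14 weeks (true total 56).* Arm A reads 1 from week 7 to week 49: 3 + 6 + 12 + 12 + 12 + 6 = 51. Arm B reads 2 then 4: 6 + 18 + 24 = 48. Close to neutral.
- *Starts 4 weeks after dosing, lasts 10 weeks (true total 40).* Arm A again gives 51. Arm B reads 1 then 3: 3 + 12 + 18 = 33. This favours Arm B.

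A smooth gamma-shaped burden with equal effect per dose, tried in a narrower and a wider shape, adds to this. For peaks 1.5 to 4 weeks after dosing, the true mean burden is equal, yet the questionnaires show Arm B worse by 0.10 to 0.34 of one dose's peak (area), or 0.13 to 0.45 (mean of post-baseline questionnaires). For peaks at 8 to 10 weeks, the spurious area gap is about 0 to 0.07 for the narrower shape. For the wider shape it is 0.26 − 0.09 = 0.17 (peak at 8 weeks) and 0.31 − 0.18 = 0.13 (peak at 10 weeks), after subtracting the true difference.

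**The case against.** A reader might infer that the HR-QoL comparison is simply biased towards the modified schedule. The documents do not support that. From week 25 onwards Arm A is closer to its last ipilimumab dose than Arm B at every questionnaire, four of the six after baseline, so persistent or late effects are read more in Arm A. The late-onset example above reverses the sign. Nor do the questionnaires always catch Arm A at the low point of its cycle: week 7 is 6 weeks after dose 1, and calling week 12 a low point presumes that symptoms have resolved by then.

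Other points also stand. Any count of doses followed by a questionnaire within 6 weeks depends on the cut-off: at 12 weeks inclusive it is four of four in both arms, and Arm B's four rest on two questionnaires, each serving two doses. Effects gone within 3 weeks are missed in Arm B too. Both arms receive nivolumab, so symptom burden does not depend on ipilimumab timing alone. Worse HR-QoL during compressed dosing is itself part of the schedule effect. HR-QoL is secondary, optional and summarised descriptively. Whether the schedule goes forward rests on grade 3 or 4 adverse reactions and 12-month PFS, and clinicians see Arm A participants 4-weekly after doses 2 to 4.

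None of this restores the missing observations. Patient-reported effects confined to the 12 weeks after Arm A's doses 2 to 4 stay unseen, and the article's argument about differential assessment does not reach them.

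**Conclusion.** The timing fact holds exactly on the planned calendar: lags of 6, 12, 12 and 12 weeks in Arm A against 6, 3, 6 and 3 weeks in Arm B. It undercuts the stated aim of reporting side-effect severity and trajectory in both schedules and of comparing these with clinician reports.

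The direction of any bias is conditional. Early, transient effects would produce a spurious advantage for the modified schedule, the direction hypothesised. With late or persistent effects the advantage shrinks or can reverse. Its size cannot be derived from the article.

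This rests on week 1 being the first dose, on dosing to plan (delays would loosen the alignment), and on questionnaire recall periods, which the article does not give, being short relative to 12 weeks. The primary endpoint is not affected. This is a cheap improvement to a secondary outcome, not a threat to the trial's main conclusion.

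**What to change.** Add questionnaires in both arms about 4 weeks after Arm A's later doses, for example at weeks 17, 29 and 41, with a window of about 1 week. In Arm A these weeks fall on the 4-weekly visits counted from week 13. If Arm B's 4-weekly visits are counted from week 16, its nearest are weeks 16, 28 and 40, which the window covers.

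In the 5-week example above, the areas move from 0 (A) and 15 (B) to 3 × (2 + 4) = 18 and 3 + 6 + 2 = 11, against a true 20. In the 8-week example they move from 6 and 30 to 6 + 18 = 24 and 6 + 12 + 6 + 4 = 28, against a true 32. The added points do not guarantee an unbiased summary, but the intervals are no longer blank.

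Keep the randomised comparison at common calendar times as the main HR-QoL analysis. Any analysis by weeks since the last ipilimumab dose should be supportive only: it conditions on doses received after randomisation, and later-dose data come only from participants still on treatment.

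If the calendar stays, state that HR-QoL and patient-reported effects after Arm A's doses 2 to 4 are measured only at the end of each 12-week interval, so a favourable result for Arm A cannot exclude missed transient effects.

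The cost is a protocol amendment and up to three extra questionnaires per participant in an optional sub-study, with a modest respondent burden. The statement alone costs nothing.

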#### Translational study

The PRISM trial incorporates a strong translational element that seeks to explore circulating and tissue based predictive biomarkers of response to immunotherapy in patients with mRCC. The identification of such markers represents a research priority. Samples of plasma, serum and cell-free DNA will be collected in all consenting patients at baseline, weeks 7, 13 (selected to coincide with clinic visits) and at disease progression. Samples will be processed according to strict standard operating procedures (SOPs) defined within an associated trial-specific translational manual and all storage kit materials supplied centrally including barcoded blood tubes. In select centres, peripheral blood mononuclear cells (PBMCs) will also be collected from participants at the same time-points. Where available, an archival formalin-fixed paraffin embedded tissue block from nephrectomised participants will also be requested.

